### Possible limitations and strengths

Generally, quasi-experimental pre- and post-intervention designs are research methods that lack the random assignment of participants to groups, which is a characteristic of true experimental designs. But in our study, the beneficiary families in each study arm (intervention and control) will be selected randomly from the available list of Sehat Sahulat program beneficiary families from the four (4) peri-urban/rural Union Councils of Islamabad Capital Territory (ICT). However, the intervention and control of private-sector-owned primary healthcare facilities will be selected conveniently in the areas where similar primary healthcare public sector facilities are unavailable, and there is a scarcity of established private-sector PHC facilities. Nonetheless, the pre-post intervention design with control is internationally accredited when controlled experimental trials are not feasible due to logistic, financial, or other ethical reasons. While these designs have their strengths, they also come with limitations. Here are some considerations; for example, the quasi-experimental designs allow researchers to study interventions in natural settings. We will ensure no spillover within different intervention areas by choosing areas at a minimum distance from each other. The difference in cultural background of participants from the intervention and control areas can become a potential limitation. However, since the intervention and control areas are located within the same city, we believe the differences would be minimal and, consequently, have a limited impact on the study findings. Another potential limitation can be the presence of competing health providers providing similar primary health care services operating within the areas of project health providers. Selecting a similar healthcare facility for the project where no other service providers exist is difficult. To address this limitation, we will use the control group to assess the impact of routine practice in health facilities toward primary healthcare services, including family planning and sexual reproductive health services, anticipating that any increase in outcomes in our study will be due to the project intervention(s). We will conduct evaluation activities by hiring an external consultant and informing participants about the study’s purpose and confidentiality before collecting data. During regular monitoring from the research team, some random visits will be made to check the reliability of data.

The validity is often compromised in quasi-experimental designs; however, our study will use statistical techniques and control measures to strengthen its validity, such as developing a study protocol as a standardized way to conduct the study to prevent researcher, instrumentation, or testing biases. When everyone follows the specific procedures, you can be more confident that the results will be valid. We will carefully select the control facility and justify the choice of the control group, ensuring that the control group is comparable to the intervention group in terms of relevant characteristics. A matched pre-post design would have been a stronger study design to compare behaviors of the same sample, as it will allow controlling for unobserved confounders such as to help address selection bias issues, control baseline differences and improve group comparability. Through Difference-in-Differences (DiD) analysis, we will compare outcome changes between the intervention and control groups, accounting for pre-existing trends. This will help control external factors that may affect both groups similarly. We will conduct validity checks for balance in covariates between groups before and after matching or weighting procedures. We will also provide clear and transparent reporting of methods, measures, and results to enhance the credibility and replicability of the study. In addition, respondents may have faced difficulties in answering questions or recall bias that captured information about their past experiences, such as information provided by the service provider about side effects at the time of method uptake, decision making and source of referral to the health facility or where the contraceptive method was adopted, exact time and discontinuation of method etc. Hence, whenever possible, we will try to supplement self-reported data with objective measures to validate the information provided by participants. Or to use standardized instruments and validated questionnaires to enhance the reliability of data collection.

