**Methods and analysis:**

A 24-month research study is proposed with a 12-month intervention period using a mixed method, two-arm, prospective, quasi-experimental controlled before and after design with a sample of 863 beneficiary families from each study arm, i.e., intervention and control groups (*N* = 1726) will be selected through randomization at the selected beneficiary family/household level from four peri-urban Union Councils of ICT where no public sector PHC-level facility exists. All ethical considerations will be assured, along with quality assurance strategies. Quantitative pre/post surveys and third-party monitoring are proposed to measure the intervention outcomes. Qualitative inquiry with beneficiaries, general practitioners and policymakers will assess their knowledge and practices.

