#### Study area

The study will be conducted in four (4) union councils (UCs) of ICT of Pakistan. Intervention and control arms will be assigned based on UCs selected for the study. The following are criteria for UC identification: (1) UC with sufficient residents of existing SSP beneficiaries, (2) UC in rural classified areas of ICT, (3) UC in which there is no public sector PHC level facility such as a Basic Health Unit (BHU), and presence of a network of private sector managed registered General Practitioners (GPs) providing primary healthcare services within identified UCs.

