### Quantitative household surveys

Before initiating the intervention, a household-based baseline survey is proposed that will cover not only the study population but also a subset of the general population from the same catchment who do not have the provision of any public or private sector health insurance. Findings will explore and explain health-related expenses and payment mechanisms if practiced or that exist other than the fee for service paid through OOP by clients in the study catchment area. The baseline survey will assess the prevalence of study indicators, document socio-economic and demographic information, out-of-pocket health expenditure, and document KAP regarding existing inpatient coverage and access and uptake of health services. A household-based endline survey at the end of 12 months of the intervention will help assess study outcomes – the impact of the outpatient services model on knowledge, attitude, and practice regarding health insurance, access, and uptake of outpatient services at the PHC level, user satisfaction, treatment outcomes, OOP health expenditure and financial protection.

Study participants for baseline and end-line assessment across the intervention and comparison arm will be selected randomly from the list frame of the SSP. Using quantitative and qualitative techniques, data collection methods will include a population-based household survey, providers’ assessment, and specific qualitative inquiry during the intervention, routine services, client satisfaction, and monitoring (clinical quality assessment) data will be done similarly to a previous study using the same design (50).

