#### Data analysis

The quantitative data analysis will focus on the combined effect of the complete package of interventions and the outcome(s) rather than exploring each component. Quantitative data will be analyzed through SPSS Software using descriptive and inferential statistics. The main outcome variables will be increased access, uptake, satisfaction, contraceptive prevalence, and reduction in OOP expenditure. Difference-in-differences (DiD) estimation will compare key outcome variables between the intervention and control group pre- and post-intervention (51). It will also measure the intervention effect on any subgroups in the intervention/control groups by comparing key outcome variables between beneficiaries in the intervention and control groups.

For the qualitative data, content and thematic analysis will be done in Nvivo Software version 11. Codes will be developed after reading the transcripts without losing the context. For qualitative analyses, transcripts will be read several times to understand the respondents’ in-depth experiences and views. ‘Meaning units’ that mirror statements will be identified as per the topic guide by highlighting phrases in the transcripts, which will be ‘condensed’, and after that ‘, codes’ will be identified from the ‘condensed meaning units’ without losing the context. Finally, the research team will review the codes independently and group similar codes into sub-categories and categories. From the categories, themes and sub-themes will be identified after systematically analyzing the commonalities, variations, and disagreements. We will further analyse data with a focus on the description and interpretation of message meaning and concepts to validate the study’s findings. Quantitative and qualitative data will be triangulated to provide comprehensive information about the impact of the research intervention. Figure 3 describes the components of the data synthesis plan envisaged for the project.

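### With one baseline and one endline survey, the difference-in-differences analysis cannot account for pre-existing trends; it assumes they are parallel, and the protocol should say so

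*Protocol article*

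**What the plan says.** The abstract describes the quantitative design as a pre/post one: "Quantitative pre/post surveys and third-party monitoring are proposed to measure the intervention outcomes". The section Quantitative household surveys gives the timing. There is one wave before the start ("Before initiating the intervention, a household-based baseline survey is proposed") and one after ("A household-based endline survey at the end of 12 months of the intervention will help assess study outcomes"). The section Data analysis defines the estimator: "Difference-in-differences (DiD) estimation will compare key outcome variables between the intervention and control group pre- and post-intervention".

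The section Possible limitations and strengths describes what this estimator achieves: "we will compare outcome changes between the intervention and control groups, accounting for pre-existing trends". The next sentence adds: "This will help control external factors that may affect both groups similarly". The same section mentions covariate balance checks around matching or weighting. Earlier in that section, competing providers are named as a limitation. The answer given is to use the control group, "anticipating that any increase in outcomes in our study will be due to the project intervention(s".

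Arms follow geography. The section Study area says: "Intervention and control arms will be assigned based on UCs selected for the study". There are four UCs, and the limitations section says that the facilities are chosen by convenience.

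**The concern.** A reader of the limitations section would conclude that the analysis protects against arms that were already diverging before the project began. To estimate or adjust for an arm-specific trend, outcomes are needed at two or more times before the intervention. The article describes one. No second pre-intervention wave, historical series or pre-trend check appears. Routine service, satisfaction and monitoring data are described as collected during the intervention, so they give no pre-period either.

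This matters because families are sampled at random within UCs but are not randomised to exposure: the arm is fixed by the UC. With four UCs and conveniently chosen facilities, a different local course in one arm is a plausible alternative explanation for a difference in change. Competing providers are an example. If one opens or closes in the UCs of one arm only, the control group does not remove the effect. The study is meant to inform scale-up, so readers should know which assumption the causal conclusion rests on.

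**Working it through.** **The plan's own figures.** Section Study population and sample size: 50% at baseline, a 10-point change, 80% power, significance level 0.05 (two-sided reproduces the result).

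- Pooled-variance formula, no continuity correction: n = [1.96 × √(2 × 0.55 × 0.45) + 0.8416 × √(0.25 + 0.24)]² / 0.10² ≈ 387.3, so 388 per arm, as stated.
- Design effect 2 and 10% missing data: 388 × 2 / 0.9 = 862.2, so 863 per arm, as stated.

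The sample size arithmetic is not in dispute here. The 10-point change is used below only as a yardstick.

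**What two waves identify.** Let a be the control level at baseline, b the fixed arm difference, c the common change over the year, d the extra change that the intervention UCs would have had without the project, and τ the treatment effect.

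| | Baseline | Endline |
|---|---|---|
| Control | a | a + c |
| Intervention | a + b | a + b + c + d + τ |

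DiD = [(a + b + c + d + τ) − (a + b)] − [(a + c) − a] = d + τ.

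The fixed difference b and the common change c cancel; d does not. There are five parameters and four cell means, and the design matrix has rank 4, so only the sum d + τ can be estimated. With one further pre-intervention wave there are six cell means and six parameters (a, b, two time effects, a linear differential trend, τ). The rank is then 6, and a linear differential trend becomes estimable.

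**Size of the bias.** The bias equals d and does not depend on sample size. The documents give no value for d. As an assumed range, 2 to 5 points is 2/10 = 20% to 5/10 = 50% of the planned change. A drift of 10 points would look the same as the full planned effect.

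**Effect on the test (illustration).** Assume no true effect, all rates near 50%, an effective 388 families per arm and wave (the stated n before the design effect), and a within-family correlation ρ between waves of 0 to 0.7. Then SE = √[2 × (0.25 + 0.25 − 2ρ × 0.25) / 388], which is 5.08 points at ρ = 0 and 2.78 points at ρ = 0.7. The two-sided 5% test rejects with probability Φ(d/SE − 1.96) + Φ(−d/SE − 1.96):

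| Assumed drift d | Rejection, ρ = 0 | Rejection, ρ = 0.7 |
|---|---|---|
| 0 points | 5% | 5% |
| 2 points | 7% | 11% |
| 5 points | 17% | 44% |
| 10 points | 50% | 95% |

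Greater precision makes a false positive more likely when drift is present. The drift values and ρ are assumptions; the identification result needs neither.

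**The case against.** The strongest reply is that the disputed phrase should be read with the sentence after it, which limits the control to factors acting on both groups alike. On that reading the article means a shared secular trend, which a two-wave DiD does remove. This has force: the wording may be loose rather than a claim to model arm-specific trends. It does not rescue the phrase. That the arms share a trend is itself the parallel-trends assumption, and the text presents it as something the method takes care of.

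Four stronger readings are tempting, and the documents do not support them.

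- *Any rise will be credited to the project as a rule.* The article says this is anticipated, and the same sentence relies on the control group. What remains is that comparison with control supports attribution only if trends are parallel, and this is not said.
- *No matching or weighting is planned, so nothing relaxes the assumption.* The limitations section names such procedures. The short Data analysis section does not repeat them, but the details may sit in a full plan that is not shown.
- *There is no safeguard at all.* A concurrent control group with DiD removes fixed differences and common shocks. Only protection against differential drift is missing, and the article openly lists area differences, convenience selection of facilities and competing providers as limitations.
- *A drift of 2 to 5 points is to be expected.* Nothing in the documents indicates its size, or that there is any.

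It is also fair to say that DiD is a standard choice for a controlled before-and-after design. The point is not that the estimator should be replaced.

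**Conclusion.** The point holds in this form: the article credits its DiD with a property that one pre-intervention and one post-intervention survey cannot give. The estimate equals the treatment effect plus any differential drift between the intervention and control UCs, and that drift can be neither estimated nor tested from the planned surveys. This follows from the number of waves alone. A later analysis plan cannot repair it without data from before the baseline.

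How much it matters in practice is unknown. The bias is one point per point of drift; 20% to 50% of the planned change is only what an assumed 2 to 5 points would imply. Assignment by UC, convenience selection of facilities and the acknowledged competing providers make the assumption worth stating openly. They do not show that it fails.

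**What to change.** 1. In Possible limitations and strengths, replace the phrase on trends with: *DiD removes time-invariant differences and common shocks and assumes parallel trends, which cannot be tested with one baseline wave.*
2. In the same section, reword the sentence on competing providers so that a change relative to control is attributed to the project only under that assumption. Say that a change in competing providers in one arm's UCs would not be removed by the control group.
3. Carry the matching or weighting already named there, or regression adjustment, into the main DiD, using the socio-economic and demographic data collected at baseline. State its limit: it addresses drift linked to household characteristics, not drift at UC level.
4. Report the estimate and its confidence interval shifted by a prespecified range of assumed drifts (estimate − d). The drift at which the interval first touches zero is simply its lower limit. For a 10-point estimate with the standard errors above, that is 10 − 1.96 × 5.08 ≈ 0.0 points at ρ = 0 and 10 − 1.96 × 2.78 ≈ 4.6 points at ρ = 0.7.
5. Optional: if partner or insurance-programme records from before the baseline exist for both arms, compare their trends. The documents do not show that such records exist, and they may not measure the main outcomes, so this supports the assumption only indirectly.

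Items 1 and 2 cost wording only. Items 3 and 4 need a little more analysis and no new data. Item 5 depends on access to records.

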## Conclusion and knowledge contribution

Primary healthcare (PHC) plays a pivotal role in a nation’s healthcare infrastructure, acting as the initial interface for patients and delivering clinical treatment at the community level. Strengthening primary healthcare requires transitioning from a narrow focus on treating specific diseases to providing personalized, holistic, and consistent care that addresses the needs of both patients and communities, thereby decreasing dependence on professional healthcare services. The effectiveness of primary care is significantly enhanced when access to higher levels of care and services is coordinated through gatekeeping, such as referrals from primary care, or when there are financial incentives for seeking care at the primary level, like minimal or no out-of-pocket payments. Such arrangements can also improve continuity of care and ensure that specialized services are utilized optimally within the healthcare system rather than being excessively utilized for conditions that can be appropriately managed in primary care settings, thus improving overall efficiency. Therefore, primary and community health services investments are essential to ensure access to the most cost-effective interventions. However, in many countries, patients either do not seek help from or bypass primary healthcare facilities due to issues such as poor accessibility (e.g., distance to facilities and treatment costs), low quality of care (e.g., lack of clinician competence and pharmaceuticals), and weak gatekeeping mechanisms. Notably, insufficient spending on primary and community health services is often seen as a major factor contributing to inequities and inefficiencies in healthcare. Consequently, urgent attention from policymakers is crucial for integrating routine primary healthcare and establishing sustainable indigenous healthcare financing mechanisms. The proposed research study aims to explore and study a service delivery model which harnesses the private sector to deliver an essential package of health services, including sexual and reproductive health services as outpatient services under SSP, ultimately facilitating UHC. Findings will provide a blueprint referral system to reduce unnecessary hospital admissions and improve timely access to healthcare. A robust PHC system can improve population health, lower healthcare expenditure, strengthen the healthcare system, and ultimately make UHC a reality.

## Ethics statement

The study received formal ethical approval from the Research and Development Solutions, Pakistan Institutional Review Board (IRB00010843).
